## Abstract

**Background:**

Multiple rib fractures are common injuries in both the young and elderly. Rib fractures account for 10% of all trauma admissions and are seen in up to 39% of patients after thoracic trauma. With morbidity and mortality rates increasing with the number of rib fractures as well as poor quality of life at long-term follow-up, multiple rib fractures pose a serious health hazard. Operative fixation of flail chest is beneficial over nonoperative treatment regarding, among others, pneumonia and both intensive care unit (ICU) and hospital length of stay. With no high-quality evidence on the effects of multiple simple rib fracture treatment, the optimal treatment modality remains unknown. This study sets out to investigate outcome of operative fixation versus nonoperative treatment of multiple simple rib fractures.

**Methods:**

The proposed study is a multicenter randomized controlled trial. Patients will be eligible if they have three or more multiple simple rib fractures of which at least one is dislocated over one shaft width or with unbearable pain (visual analog scale (VAS) or numeric rating scale (NRS) > 6). Patients in the intervention group will be treated with open reduction and internal fixation. Pre- and postoperative care equals treatment in the control group. The control group will receive nonoperative treatment, consisting of pain management, bronchodilator inhalers, oxygen support or mechanical ventilation if needed, and pulmonary physical therapy. The primary outcome measure will be occurrence of pneumonia within 30 days after trauma. Secondary outcome measures are the need and duration of mechanical ventilation, thoracic pain and analgesics use, (recovery of) pulmonary function, hospital and ICU length of stay, thoracic injury-related and surgery-related complications and mortality, secondary interventions, quality of life, and cost-effectiveness comprising health care consumption and productivity loss. Follow-up visits will be standardized and daily during hospital admission, at 14 days and 1, 3, 6, and 12 months.

**Discussion:**

With favorable results in flail chest patients, operative treatment may also be beneficial in patients with multiple simple rib fractures. The FixCon trial will be the first study to compare clinical, functional, and economic outcome between operative fixation and nonoperative treatment for multiple simple rib fractures.

**Trial registration:**

www.trialregister.nl, NTR7248. Registered May 31, 2018.

## Background

Rib fractures are common injuries in both trauma and non-trauma centers, occurring in up to 10–39% of patients with blunt chest trauma and accounting for 10% of all trauma admissions [1–4]. With an estimated 25% of all traumatic deaths, chest trauma ranks second after head injury [3, 4]. Rib fractures are caused by high-energy trauma (HET) in the younger patients, often with concomitant injuries, and in the elderly as a result of low energy trauma (LET) [5–7]. Sustaining multiple rib fractures can result in a flail chest, defined as fracture of three or more consecutive ribs in two or more places, creating a flail segment [8, 9]. Patients may also have multiple simple rib fractures or a combination of both.

While open surgical fixation of rib fractures dates back to the 1940s, multiple rib fractures are routinely treated nonoperatively [10]. Nonoperative treatment includes pain management, oxygen support or mechanical ventilation, bronchodilator inhalers, and pulmonary physical therapy. Despite this treatment strategy, mortality and complications such as pulmonary contusion, hemopneumothorax, and pneumonia are seen in up to 34% and in 35–77% of patients, respectively [1, 2, 5, 6, 11–15]. Various studies have identified risk factors that increase mortality such as age and number of rib fractures [3, 6, 7, 11, 16–18].

Furthermore, at 2 years post-injury, up to 29% of patients have not yet returned full time to their pre-injury job and 64% of patients with isolated multiple rib fractures still experience chest wall pain [19, 20]. With incapacitating pain often accompanying traumatic rib fractures, epidural analgesics are suggested as the optimal analgesic for patients with multiple rib fractures. Two meta-analyses have shown that epidural use results in significant less pain but has no benefit regarding the length of both intensive care unit (ICU) and hospital stay, mortality, and complication rate, indicating the necessity of an optimized analgesic modality for rib fracture patients [21, 22].

Rib fractures may show the same pattern as a restrictive pulmonary disease, resulting in loss of total lung capacity which precipitates inadequate oxygenation and ventilation. Patients with rib fractures and reduced pulmonary function are more susceptible to pulmonary complications and longer length of hospital stay [23–25]. With contradicting studies on the difference in spirometry between operatively and nonoperatively treated patients with rib fractures, additional research is needed [12–14, 26–29]. While surgical treatment of flail chest patients appears to be cost-effective over nonoperative treatment, but for multiple simple rib fractures, the most cost-effective treatment modality is still unknown [30, 31].

Over the last decade, there has been an increasing number of studies suggesting superior results of open reduction and fixation (ORIF) for the stabilization of multiple rib fractures due to profitable results in traumatic flail chests compared with nonoperative management [31–34]. Several studies with flail and non-flail chest patients combined have shown promising effects of ORIF with less pneumonia, less hemo- and pneumothorax, shorter need for mechanical ventilation, lower mortality, shorter length of hospital and ICU stay, and quicker return to normal activity [15, 28, 35–38].

As only two studies, both retrospective cohort studies with small sample sizes and short follow-up, have singularly focused on operative versus nonoperative management of multiple simple rib fractures, definitive proof for the optimal treatment of multiple simple rib fractures is not achieved yet [9, 14, 39–41].

Therefore, the aim of this multicenter randomized controlled trial is to investigate the effect of ORIF versus nonoperative treatment in patients who sustained multiple simple fractured ribs.

## Methods/design

### Objective

The primary aim of this trial is to investigate the effect of ORIF versus nonoperative treatment on the occurrence of pneumonia within 30 days after trauma in adult patients who sustained multiple simple fractured ribs. The secondary aims are to investigate the effect of treatment on the need for and duration of mechanical ventilation, level of thoracic pain and analgesics use, (recovery of) pulmonary function, hospital and ICU length of stay, thoracic injury-related and surgery-related complications and mortality, secondary interventions, quality of life, and total costs (in-hospital and socio-economic) of treatment, health care consumption, and work absence. At the end, a cost-effectiveness analysis will be done.

### Trial design and setting

The FixCon trial is a multicenter randomized controlled trial, with a parallel group design. The following 12 hospitals in The Netherlands will participate: Amphia Ziekenhuis (Breda), Catharina Ziekenhuis (Eindhoven), Deventer Ziekenhuis (Deventer), Erasmus MC (Rotterdam), Haga Ziekenhuis (The Hague), Ikazia Ziekenhuis (Rotterdam), Isala (Zwolle), Maasstad Ziekenhuis (Rotterdam), Maastricht UMC+ (Maastricht), Rijnstate (Arnhem), Spaarne Gasthuis (Haarlem), and Zuyderland Medisch Centrum (Heerlen).

## Inclusion and exclusion criteria

The study population will consist of adults with three or more simple rib fractures after blunt force trauma. The fracture pattern will be diagnosed and delineated with a CT scan of the thorax, at least 64-slice and preferable including 3D reconstruction.

In order to be eligible to participate in this study, a patient must meet all of the following inclusion criteria:Age 18 years or olderFor any of the ribs number 4 to 10, three simple fracture ribs with either A) at least one fracture dislocated over one shaft-width; or B) unbearable pain (VAS or Numeric Rating Scale (NRS) >6 points)Blunt force traumaHospital presentation within 72 h after traumaProvision of informed consent by patient or proxy

A patient who meets any of the following criteria will be excluded from participation:Neurotraumatic changes leading to mechanical ventilation (GCS ≤ 8 at 48 h post-injury. If unable to assess full GCS due to intubation or other causes, GCS motor ≤ 4 at 48 h post-injury)Rib fractures due to cardiopulmonary resuscitationSurgical rib fixation not possible due to additional traumatic injuries (hemodynamically or pulmonary unstable, for example, based on parenchymal lung trauma) or the patient is unfit for surgery, to be decided by an ICU doctor, trauma surgeon, or anesthesiologistFlail chest, based on radiological or clinical findingsDecreased sensory or motor function due to (previous) cervical or thoracic spine failurePrevious rib fractures or pulmonary problems, requiring continuous oxygen use at home pre-traumaCongenital thoracic deformity (pectus excavatum, pectus carinatum, severe scoliosis, or kyphosis)Inhalation trauma or severe burns close to or inside the mouth or neckSurgical fixation of the ribs not feasible within 7 days after traumaPatient unwilling or unable to comply with the intervention or follow-up visit scheduleInsufficient comprehension of the Dutch language to understand the rehabilitation program and other treatment information in the judgement of the attending physicianParticipation in another surgical intervention or drug study that might influence any of the outcome parameters

### Recruitment and randomization

Eligible persons presenting to the emergency department (ED) or referred from another hospital, with multiple, simple rib fractures will be informed about the trial at the ED or at the surgical ward after admission. After explanation of the study, eligible patients will receive written information and a consent form from the attending physician, the clinical investigator, or a research assistant. Patients meeting all eligibility criteria will be recruited within 1 day after hospital admission. As surgical rib fixation appears to be most beneficial when performed within 72 h after trauma, patients are stimulated to decide within this period. However, informed consent can be given by the patient as long as rib fixation can be carried out within 1 week after trauma. Should patients not be able to sign informed consent themselves, a legal representative will receive oral and written information about the study, in the hospital, by the attending physician, the clinical investigator, or a research assistant, and will be asked to consent with participation of the patient.

After signing informed consent by patient or proxy, participants are allocated to one of the two study arms (surgical stabilization or nonoperative treatment) using a web-based randomization program that will be available 24 h a day. Allocation will be at random and concealed, in a 1:1 ratio, and will be stratified by site. Variable block sizes will be used; in each block, both treatments will be represented equally. As the intervention cannot be blinded, it will in no case be necessary to break the randomization code.

As with many surgical trials, patients and surgeons cannot be blinded for the intervention. In order to reduce bias as much as possible, a research physician or research assistant will perform the follow-up measurements using a standardized protocol. Also, the treating surgeon or ICU doctor will identify the primary outcome (i.e., pneumonia) based on the definition as mentioned under outcome measures.

Participation is on a voluntary basis and participants are allowed to withdraw from the study at any time without specifying why. The general practitioner will be informed about the patients’ participation.

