### Outcome measures

#### Primary outcome measure

The primary outcome measure is pneumonia within 30 days after trauma. In order to define pneumonia, the flowchart of the Centers of Disease Control and Prevention, based on imaging and clinical and laboratory criteria, will be followed (Fig. 1) [42]. Temperature (*T*) will be measured daily during admission. If *T* > 38.0 °C intra-auricular (or *T* > 39 °C rectal), bladder, central, or a sputum culture will be done. Also, the wound will be checked (if applicable) and a radiograph of the thorax will be made. If patients are suffering from fever at home, they will be advised to visit the outpatient clinic or emergency department. The temperature will be measured on arrival at the outpatient clinic or emergency department, and the same additional examinations will be performed. A monitor will independently review the patient’s medical files in order to ensure that the pneumonia was actually present.

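### Unblinded treating clinicians call pneumonia, and the only described check confirms that a pneumonia was present; no search for missed cases and no masking to arm is described

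*Protocol article*

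**What the plan says.** The endpoint is fixed in the Protocol article, Primary outcome measure: "The primary outcome measure is pneumonia within 30 days after trauma". The case definition is the CDC flowchart, "based on imaging and clinical and laboratory criteria, will be followed".

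**Who makes the call.** Recruitment and randomization concedes that "patients and surgeons cannot be blinded for the intervention". It then names two steps meant to limit bias. One is that research staff take the follow-up measurements under a standard protocol. The other is that "the treating surgeon or ICU doctor will identify the primary outcome (i.e., pneumonia) based on the definition" given for the outcome.

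**Who checks the call.** Primary outcome measure has a monitor independently go through the patient's "medical files in order to ensure that the pneumonia was actually present". Nothing is said about masking the monitor.

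**What limits discretion.** Temperature is taken daily during admission. Fever leads to a culture, and "the wound will be checked (if applicable) and a radiograph of the thorax will be made". After discharge the same examinations apply, but only if the patient attends: "If patients are suffering from fever at home, they will be advised to visit the outpatient clinic or emergency department". Study procedures adds that, at each follow-up visit, the coordinating researcher or an assistant records complications and secondary interventions and checks them against the medical records. Two of those visits, at 2 weeks and 1 month, are scheduled at or before day 30.

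**The concern.** The treating surgeon knows the allocation and may have performed the operation. Giving that person the classification of the primary outcome does not reduce bias in an open surgical trial. It is the exposure that an independent assessment is normally meant to remove. A definition that combines imaging, clinical signs and laboratory results narrows the judgement involved but still has to be applied by someone.

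The check described has a direction. Its purpose is to establish that a pneumonia was there, so it can remove a wrong positive call. A case that was never called is not its stated object. If one arm loses more true cases than the other, the comparison shifts and no described step shifts it back. The error would also reach the cost-effectiveness ratio, which Statistical analyses expresses as costs per pneumonia prevented.

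**Working it through.** **1. The plan's own figure.** Sample size calculation gives 35% versus 15%, two-sided α 0.05, β 0.2, and 72 per group. The pooled-variance formula without continuity correction is

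n = [1.96·√(2p̄(1−p̄)) + 0.8416·√(p₁(1−p₁) + p₂(1−p₂))]² / (p₁−p₂)², with p̄ = (0.35 + 0.15)/2 = 0.25.

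This is [1.96·√0.375 + 0.8416·√0.355]² / 0.04 = [1.200 + 0.501]² / 0.04 ≈ 72.4. The stated 72 is reproduced (73 if rounded up), so 72 and 90 per group serve as the working sizes.

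**2. Inputs that the documents do not give.** The miss rates are assumptions. So is a common true rate under no treatment effect. I take 25%, the midpoint of the planning rates, and vary it. I also assume that no false positives remain after the monitor's review.

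**3. Method.** With true rate p in both arms and missed fractions m₁ and m₂, the recorded rates are p(1−m₁) and p(1−m₂). The uncorrected chi-squared test rejects when |x₁−x₂|/n ÷ √(2p̂(1−p̂)/n) > 1.96, where p̂ is the pooled observed rate. The rejection probability is the sum of Bin(x₁; n, p(1−m₁))·Bin(x₂; n, p(1−m₂)) over all such pairs.

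**4. Misses in one arm only, no true effect (two-sided rejection probability).**

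| True rate | Per arm | 10% missed | 20% missed | 30% missed |
|---|---|---|---|---|
| 25% | 72 | 6.7% | 11.4% | 20.0% |
| 25% | 90 | 6.7% | 12.4% | 23.0% |
| 35% | 72 | 7.2% | 14.7% | 28.3% |
| 35% | 90 | 7.9% | 17.2% | 33.7% |
| 15% | 72 | 5.7% | 8.1% | 12.6% |
| 15% | 90 | 5.8% | 8.9% | 14.6% |

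At a 25% rate the recorded rates in the affected arm are 0.25 × 0.9 = 22.5%, 0.25 × 0.8 = 20% and 0.25 × 0.7 = 17.5%. In patients, a 20% miss at 90 per arm is 90 × 0.25 × 0.20 = 4.5 expected cases. Most of the rejections favour the arm with the missed cases.

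**5. Misses in both arms, 25% true rate, 72 to 90 per arm.** With 10% against 20%, or 20% against 30%, the rejection probability is 6.8–7.0%. With equal misses it is 4.9–5.2%, so the error rate stays at about its nominal level.

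**6. The opposite direction.** If the planned effect is real (35% versus 15%) and 20% of nonoperative cases are missed, the recorded control rate is 0.35 × 0.8 = 28%. Exact power at 72 per group then falls from 81% to 49%.

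**7. What the check changes.** A review that only removes false positives alters none of these figures, because false positives were already set to zero.

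**The case against.** Four arguments stand against making more of this.

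- **Scope of the review.** A reader might infer that the monitor opens only files with a recorded pneumonia, so that an under-called case is never corrected. The text does not say that. It gives the purpose of the review and sets no limit on which files are opened. A fuller protocol or monitoring plan may settle both scope and masking. This stands, and it limits the point to what is described.
- **Other safeguards.** The daily temperature, the numeric fever threshold and the resulting examinations do not differ by arm, and research staff verify complications in the records within the 30-day window. Antibiotic treatment is also recorded as a secondary intervention. These lower the risk. However, the work-up produces data that the treating doctor still classifies, and the staff checks are not linked to the primary-outcome classification or said to be masked.
- **Direction.** A reader might infer a false benefit for ORIF. Nothing in the document shows that ORIF cases would be under-called. Changes on imaging after surgery could equally lead to over-calling in that arm. The flowchart figure is not reproduced in the text available, so the room for judgement cannot be measured.
- **Size.** The 20–23% figure needs a 30-point gap in missed cases with perfect detection in the other arm. With misses in both arms and a 10-point gap it is about 7%. This stands too.

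These arguments do not remove the core. The plan makes a treating clinician's call the primary outcome, counts that as bias reduction, and describes a check aimed at confirming pneumonia.

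**Conclusion.** The point holds as an uncorrected risk of differential misclassification, not as demonstrated bias. Surgeons are expressly unblinded. The ICU doctor is not expressly called so, but treats the patient, and no masking is described. The described endpoint check confirms pneumonia, and no described step looks for missed cases and feeds them into the classification.

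The document does not support saying that missed cases can never come to light, or that the error must favour operation. Under the stated assumptions (25% true rate in both arms, no residual false positives), the false-positive rate ranges from about 5% with equal misses, through about 7% for a 10-point gap with misses in both arms, to 20–23% if 30% of cases are missed in one arm only. The miss rates are illustrative. The change is worth making because it is cheap and concerns the primary outcome.

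**What to change.** State in the protocol that the existing monitor applies the CDC flowchart to every patient in both arms who had fever, a culture, chest imaging or antibiotics within 30 days, whether or not pneumonia was recorded. The monitor should not be told the allocation where that is feasible. Use this classification for the primary analysis and the treating doctor's call as a sensitivity analysis. If the monitor already reviews all files, one sentence saying so settles the scope; masking and whose classification counts would still need stating.

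The antibiotic trigger should not count the single preoperative prophylactic dose in the operative protocol, or it would select every operated patient. Reviewing all files avoids this.

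**Cost.** The monitor reviews more files, at most 180, with no new tests and no change to care. Full redaction across 12 hospitals would need work by someone else, so masking should go only as far as is practical. It will be incomplete, because files and imaging reports may reveal surgery. Cultures, imaging and antibiotics are also partly ordered by unblinded clinicians, so a difference in work-up between the arms would not be fully removed.

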## Nonoperative allocation

Nonoperative treatment will consist of optimal pain treatment, supportive oxygen or ventilation if needed, early mobilization, Salbutamol/Atrovent spray, and physical therapy for optimizing ventilation. Without definitive proof for the best protocol, each participating center is allowed to use its local protocol for interpleural drainage use, mechanical ventilation, and pain control. Although this may introduce some heterogeneity across hospitals, it benefits extrapolation of the results. Critical elements of the nonoperative treatment will be recorded.

## Operative allocation

Preoperative treatment is the same as in the nonoperative treatment group. ORIF should be preferably carried out within 72 h after trauma, but fixation within 1 week will not lead to exclusion. The surgical fixation will be conducted by a senior fracture management surgeon who has participated in at least five rib fracture fixation procedures. A surgeon in training with limited experience in rib fixation is allowed to work under supervision of an experienced surgeon.

Patients allocated to the surgical group will undergo ORIF using plates and/or splints. The decision on what rib fixation system to use is to the discretion of the treating surgeon, provided that the fixation system is CE-mark approved for rib fixation. Each system will be used according to the supplier’s protocol. The patient will receive an intravenous single prophylactic dose of a third-generation cephalosporin preoperatively. The incision will be planned, based preferably on a preoperative 3D reconstruction of the thoracic cage. The positioning of the patient and number of ribs fixated will be left to the preference of the operating surgeon. A minimally invasive technique will not lead to exclusion of the study. The ribs will be visualized using a muscle-sparing approach. After removing interpositioning tissue, fracture reduction will be carried out and the rib fixation device will be positioned and fixated. The use of interpleural space rinsing with warmed NaCl 0.9% or thoracoscopic visualization during rib fixation will be left to the judgement of the surgeon. If indicated, an interpleural drain is percutaneously placed in dorsocaudal direction, apart from the surgical wound. The wound is closed, using a wound drain if needed.

After surgery, the patient will be admitted to the ward or ICU depending on his/her clinical state. Participating hospitals are allowed to use their local protocol for interpleural and wound drainage. Postoperative physical therapy and supportive treatment may be prolonged if needed. Postoperative care and preoperative treatment are the same as for nonoperative management. Critical elements of the operative treatment will be recorded.

